## Methods/Design

### Objectives

The primary objective of this study is to compare a tailored discharge planning and case management approach for patients who are frequently admitted to Alice Springs Hospital with patients receiving usual care using the primary outcome of decreased readmissions. To do this we will:i.Develop and evaluate a multidimensional discharge planning and case-management approach aimed at reducing all-cause readmissionsii.Identify factors which predict readmission and subsequent mortality and thus factors which identify patients who are most likely to benefit from this interventioniii.Evaluate the efficacy and cost-effectiveness of this tailored case management-based approach

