### Exclusion criteria

Anticipated life expectancy of 12 months or less based on treating specialist assessmentStage 5 chronic kidney disease (eGFR < 15ml/min or receiving renal replacement therapy)Solid organ transplant (including renal transplant)Active palliative care involvementPreviously been enrolled in the study (such subjects will have on-going care as per their original study allocation)

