### Outcome measures

Determination of endpoints will occur at 12 months from enrolment and will be based on the CONSORT Statement [30] including an intention-to-treat analysis. Determination of endpoints will take account of censuring relating to participant survival or being lost to follow-up and will be blinded and subject to secondary panel review for adjudication where doubt exists regarding interpretation of end point definitions.

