### Sample size

Sample size analysis is based on data derived from Alice Springs Hospital admission data during 2013 regarding patients suitable for inclusion in this study. Alice Springs Hospital data indicates more than 300 individual patients were admitted to Alice Springs hospital over the preceding 12 months who would meet inclusion criteria for this study. Overall these patients had a mean number of admissions of eight per year (standard deviation four). Based on an alpha of 0.05 and beta of 0.1 (power of 90%) and a clinically significant reduction in the number of readmissions of 25% the calculated sample size (control and intervention arms) will be 210 with 70 in the intervention arm and 140 in the control arm (ratio 1:2) [24].

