### Statistical analysis

Statistical analysis of the primary end point will be based on bivariate analysis for continuous variables for inpatient days and chi square and survival analysis for all-cause mortality. Multivariate analysis will be utilised to develop predictive equations for risk of readmission and survival utilising baseline data including functional assessment results (Resource Utilization Groups–Activities of Daily Living (RUG-ADL) [31, 32], Australian Modified Karnofsky Performance Scale (AKPS) [33] and objective [6MWT, SRT [34, 35]), measures of function, co-morbidities (including severity), demographics and anthropometry. Analysis will be based on intention to treat. If data is found to be missing, this item will not be included which will be associated with deletion of cases for the prescribed elements.

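### The planned survival equation has 11 named candidate predictors, and about 15 to 17 in all, in 210 people followed for 12 months; without shrinkage it would be materially overfitted.

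*Protocol article*

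**What the plan says.** All references are to the protocol article.

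- **Statistical analysis.** "Multivariate analysis will be utilised to develop predictive equations for risk of readmission and survival utilising baseline data". The sources named are RUG-ADL, AKPS, the six minute walk test, the sit-rise test, co-morbidities with their severity, demographics and anthropometry. Missing items lead to deletion of cases.
- **Objectives, item ii.** "Identify factors which predict readmission and subsequent mortality", and through these the patients most likely to benefit.
- **Baseline data.** Seven co-morbidity groups are itemised: coronary heart disease, heart failure, rheumatic heart disease, diabetes, COPD/bronchiectasis, sleep-related disorders and musculoskeletal disorders. Weight, height and BMI are listed. Ethnicity is the only demographic item named.
- **Outcome measures.** "Determination of endpoints will occur at 12 months from enrolment".
- **Exclusion criteria.** "Anticipated life expectancy of 12 months or less", as judged by the treating specialist. Recruitment strategies and consent adds that a patient remains potentially eligible when the clinician is unsure.
- **Sample size.** The total "will be 210 with 70 in the intervention arm and 140 in the control arm (ratio 1:2"). It is derived from a "mean number of admissions of eight per year (standard deviation four") and "a clinically significant reduction in the number of readmissions of 25" per cent. It makes no reference to deaths or to the prediction equations.

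The article gives no expected mortality.

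**The concern.** One broad list of baseline data is offered for two outcomes that differ greatly in how much information they carry. At a planning mean of eight admissions per person-year, readmissions are plentiful. Deaths are limited three ways: by a sample sized for something else, by a 12-month horizon, and by an entry rule that removes people expected to die within that horizon. Case deletion then removes further participants, and with them some of the deaths.

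If a conventional multivariable survival model is fitted to the listed predictors, it will partly describe chance features of this cohort. Its accuracy in the trial's own data will look better than it is, and its predicted risks will be too extreme in new patients. At stake is the mortality half of objective ii, which is meant to inform who should be offered the programme.

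**Working it through.** **1. The plan's own figure.** The article has no sample size for prediction, so the only figure to reproduce is 210. With a difference of 25% × 8 = 2 admissions, SD 4, two-sided alpha 0.05, 90% power and 2:1 allocation:

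n(control) = (1.960 + 1.282)² × 4² × (1 + 1/0.5) / 2² = 10.507 × 16 × 3 / 4 = 126.1, so 127. The intervention arm needs 64, and the total is 191.

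Rounding up to whole blocks of 21 gives ten blocks, which is 210 (140 + 70). Power at 140/70 is 92.7%. The stated size is therefore adequate for its own purpose, and nothing below depends on the gap between 191 and 210.

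**2. Candidate predictors.**

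- Functional measures: 4 (named).
- Co-morbidity groups: 7 (named), before any severity grading.
- Subtotal explicitly named: 11.
- Demographics: about 3 (ethnicity named; age and sex assumed).
- Anthropometry: 1 (BMI only) to 3.
- Total: 15 to 17. I use 16 as the working value.

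**3. Deaths and deaths per candidate.** Deaths = 210 × mortality. Mortality is an assumption, so a range is shown.

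| Assumed 12-month mortality | Deaths | Per candidate, 11 | Per candidate, 16 |
|---|---|---|---|
| 5% | 10.5 | 1.0 | 0.7 |
| 10% | 21 | 1.9 | 1.3 |
| 15% | 31.5 | 2.9 | 2.0 |
| 20% | 42 | 3.8 | 2.6 |
| 30% | 63 | 5.7 | 3.9 |

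Five deaths per candidate would need 5 × 16 = 80 deaths (80/210 = 38% mortality) with 16 candidates, or 5 × 11 = 55 deaths (26%) with 11. Ten per candidate would need 160 deaths (76%) or 110 deaths (52%).

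**4. Expected shrinkage.** Treat 12-month death as binary. Let R² be the Cox–Snell value, assumed at 15% or 30% of its maximum, and p the number of candidates. Then LR = −N ln(1 − R²), and expected shrinkage is S = LR/(LR + p).

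Example at 10% mortality: the maximum R² is 0.478, so R² = 0.15 × 0.478 = 0.0717. LR = 210 × 0.0744 = 15.6, and S = 15.6/31.6 = 0.49.

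Over 5 to 30% mortality and both R² assumptions, S with 16 candidates runs from 0.40 to 0.76. The usual target is 0.9. The size needed for that, n = p/[(S − 1) ln(1 − R²/S)] with S = 0.9, runs from about 600 to about 2,850 participants.

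**5. Simulation.** N = 210, with independent standard-normal predictors. Four are prognostic (log-odds ratios 0.45, 0.35, 0.35 and 0.25 per SD; true AUC about 0.70). An unpenalised logistic model is tested in 20,000 new subjects. Medians with 16 candidates:

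| Mortality | Apparent AUC | AUC in new patients | Calibration slope |
|---|---|---|---|
| 5% | 0.87 | 0.59 | 0.15 |
| 10% | 0.81 | 0.61 | 0.28 |
| 15% | 0.78 | 0.62 | 0.34 |
| 20% | 0.76 | 0.64 | 0.44 |
| 30% | 0.75 | 0.64 | 0.47 |

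With only the 11 named items, the slope runs from 0.25 (5% mortality) to 0.59 (30%). Apparent AUC falls to about 0.73 at the favourable end, and AUC in new patients reaches about 0.65. Serious overfitting persists when the four prognostic predictors are correlated.

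A model holding only the four truly prognostic predictors gives 0.74/0.66/0.55 at 5% mortality and 0.72/0.67/0.70 at 10% (same three measures). Ridge shrinkage on all 16 raises the slope to about 0.8.

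**The case against.** **Model form is not fixed.** The sentence names sources of data. It does not say that every item enters the survival equation, and an analysis plan not shown could limit or penalise the predictors. This stands as a caution, and the absence of such detail from an article is not the point here. However, the number of candidates examined drives overfitting, so data-driven selection from the list would not cure it. Only pre-selection or shrinkage would.

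**The count of 16 is partly built on assumptions.** This is correct. Age and sex are assumed, BMI is a function of weight and height, and co-morbidity could be reduced to one score. For that reason 11 is carried alongside 16, and the conclusion holds at both.

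**Survival may be followed for longer.** Study design has survival data collected at the end of the study, recruitment lasts 24 months, and objective ii sets no time limit. The schedule table nevertheless puts close-out at 12 months. Longer follow-up would add deaths, but probably not enough for 16 terms without shrinkage.

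**The simulation is harsh.** Twelve of its 16 predictors are noise, and its four-predictor comparator knows the truth in advance. Both criticisms are fair. Even that comparator has a slope of only 0.55 to 0.70 at 5 to 10% mortality, so a short list alone is not a complete remedy.

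**Stronger readings to avoid.** A reader might infer that the cohort is selected to survive, so that deaths will be negligible. Patients with an uncertain prognosis are eligible, and the article itself plans to check how accurate clinicians' prognoses are. A reader might also infer that the equation would be little better than noise. An AUC of 0.59 to 0.65 in new patients, against a true 0.70, is a real loss but does not support that.

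**Conclusion.** The point holds for the survival equation. Using the listed predictors without shrinkage gives roughly 0.7 to 5.7 deaths per candidate over an assumed 5 to 30% mortality. The calibration slope is about 0.15 to 0.6, and the AUC is overstated (about 0.73 to 0.87 apparent, about 0.59 to 0.65 in new patients). Case deletion would make this worse by an amount the article does not allow one to calculate.

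The figures rest on four assumptions: the mortality range, a true AUC near 0.70, a binary 12-month outcome standing in for survival time, and 11 to 17 candidates. The direction of the conclusion does not turn on the exact mortality. With 16 candidates, even five deaths per candidate would need 38% of the cohort to die within a year.

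The scope is limited to the mortality part of objective ii. A reader might extend the criticism to the readmission equation, the sample size or the trial's main result. The documents do not support that: admissions are frequent, 210 is enough for the admissions comparison, and the randomised analysis does not use these equations. It is worth correcting before analysis, but it is not a threat to the primary conclusion.

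**What to change.** Separate the two equations in the Statistical analysis section. The broad predictor list can stay for readmission. For survival, choose one of these before outcomes are examined:

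- ridge-penalised Cox regression on the listed predictors; or
- a few predictors fixed in advance from the baseline data being collected, for example age, AKPS and one co-morbidity summary, also with shrinkage.

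Prior admission count is best left out of that short list. It is not among the itemised baseline data, and the entry criteria restrict its range.

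In either case, report bootstrap optimism-corrected discrimination and calibration slope, give the number of deaths and complete cases used, and label the survival equation exploratory.

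The cost is revised analysis wording and a little programming; no new data are needed. The downside is that fewer individual mortality predictors can be reported, and the headline accuracy will be lower than an uncorrected model would show.

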### Health economic analyses

The use of all health care resources will be measured and multiplied by the respective unit costs. In general, hospital admissions typically incur higher costs for the initial period when diagnostic tests and surgical procedures are undertaken. The later days stay are relatively lower cost with little more than hotel costs incurred. The use of National Weighted Activity Units will allow standardisation and categorisation of each readmission episode into fixed and variable costs [37]. Fixed costs are those that all surviving patients incur irrespective of their length of stay, whilst variable costs are a per diem cost and are dependent on the length of stay. The total costs will be calculated as the variable costs multiplied by the length of stay plus the fixed cost. Fixed costs will include components for the emergency department, pathology, imaging, allied health professional input, pharmacy, critical care, prostheses, operating room procedures and specialist procedure suites. Per diem costs will include those for medical staff, nursing staff, non-clinical staff, staff on-costs, supplies, hotel costs (e.g. meals), and depreciation. Length of stay in intensive care and critical care units (ICU/CCU), as well overall length of stay will be ascertained. Accordingly, costs will be calculated using fixed costs plus the mean per diem cost for ICU/CCU plus the per diem cost for a general ward multiplied by the lengths of stay in each facility. Costs for providing the intervention will be calculated based on time spent by all team members with each patient. Costs for use of primary care services will be based on number of visits multiplied by a standard cost for a GP visit at the time [38].

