**Methods:**

This randomised control trial compares a tailored, multidimensional transitional care package to usual care. The objective is to evaluate the efficacy of the transitional care package for Indigenous and non-Indigenous Australian patients with chronic diseases at risk of recurrent readmission with the aim of reducing readmission rates and improving transition to primary care in a remote setting. Patients will be recruited from medical and surgical admissions to Alice Springs Hospital and will be followed for 12 months. The primary outcome measure will be number of admissions to hospital with secondary outcomes including number of emergency department presentations, number of ICU admissions, days alive and out of hospital, time to primary care review post discharge and cost-effectiveness.

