#### Secondary endpoints

i.Rate of associated all-cause hospital inpatient days (/months follow-up)ii.Overall rate of emergency department attendances (/months follow-up)iii.Days alive and out-of-hospital (including linkage with NT Government Death notifications) (/months of follow-up) according to actual versus maximal possible event-free days of survivaliv.Number of ICU/HDU admissions and bed days (/months of follow-up)v.Time to first primary health care review following hospital discharge (days or mean days if more than one admission)vi.Health care costs (see Health Economic Analyses below)

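### Cost-effectiveness is an objective, but the listed endpoint and the costing section cover costs only, and fixed costs are defined for survivors alone

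*Protocol article*

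**What the plan says.** The Abstract (Methods) ends its list of secondary outcomes with "time to primary care review post discharge and cost-effectiveness". Objectives, item iii, reads "Evaluate the efficacy and cost-effectiveness of this tailored case management-based approach".

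The endpoint list is narrower. Secondary endpoint vi is "Health care costs (see Health Economic Analyses below", with no effect, ratio or net benefit attached. Unlike endpoints i to iv, it carries no per-month-of-follow-up denominator.

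The section it points to, Health economic analyses, is detailed about how costs are built. It starts from the principle "The use of all health care resources will be measured and multiplied by the respective unit costs" and splits each readmission episode into fixed and variable parts. On the fixed part it says "Fixed costs are those that all surviving patients incur irrespective of their length of stay", and then "The total costs will be calculated as the variable costs multiplied by the length of stay plus the fixed cost". A second formula separates intensive care from ward days and weights each by the days spent there: "costs will be calculated using fixed costs plus the mean per diem cost for ICU/CCU plus the per diem cost for a general ward". The components listed as fixed include the emergency department, pathology, imaging, critical care and operating room procedures. Team time and primary care visits are costed as well. The section does not say what the costs will be compared with.

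Outcome measures adds a general statement that endpoint determination will allow for censoring through death or loss to follow-up. It does not say how this applies to costs.

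**The concern.** There are two separate points.

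First, the objective and the endpoint do not match. Cost-effectiveness needs a cost difference and an effect difference; the endpoint and its supporting section supply only the first. A cost comparison alone settles the question only if the package is no dearer, or if outcomes are equal. The second condition is the opposite of the trial's hypothesis. If the package avoids admissions at a net cost, a cost endpoint can only report that it costs more.

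Second, the fixed-cost definition is wrong as worded. A patient who dies in hospital has also used the emergency department, imaging, theatre or critical care. Restricting these costs to survivors makes a fatal admission look cheaper than it was, and the error leans towards whichever arm has more in-hospital deaths.

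**Working it through.** The article gives no unit cost, death rate or cost-effectiveness figure, so there is no stated figure to reproduce. The check compares the sections and then sizes the wording problem on stated assumptions.

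**Sections side by side**
- Abstract and Objectives iii: cost-effectiveness.
- Secondary endpoint vi: health care costs.
- Health economic analyses: hospital, intervention and primary care costs; no effect measure.
- Effects available elsewhere: admissions (primary endpoint) and days alive and out of hospital (secondary endpoint iii), which counts death as lost time.

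**Why cost alone is not enough**
- Sample size section: mean 8 admissions a year and a 25% reduction, so 0.25 × 8 = 2 admissions avoided.
- Let C be the mean cost of one admission. Planned gross saving = 2C per participant.
- Suppose the package costs K admission-equivalents per participant (K is an assumption). Net cost = (K − 2)C; cost per admission avoided = (K − 2)C / 2.
- K = 2.5 gives 0.5C / 2 = 0.25C. K = 3 gives 1C / 2 = 0.5C.
- For any K above 2, the cost endpoint alone says only that the package is dearer. The ratio comes from data already planned, but the endpoint does not call for it.

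**Survivor wording, one fatal admission**
- With fixed cost F and length of stay L, both in per-diem units, full cost is F + L; the literal reading leaves L. The understatement is F / (F + L).
- Assumed F = 2, 5 or 10 and L = 3, 5 or 10: smallest 2 / 12 = 17%, largest 10 / 13 = 77%.

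**Survivor wording, difference between arms**
- Assumptions: mortality differs by 5 points; 50% to 80% of deaths occur in hospital; the fixed share is 40% to 60% of an admission's cost; a terminal admission costs 1 to 3 times the average.
- Low: 0.05 × 0.5 × 0.4 × 1 = 0.010C. High: 0.05 × 0.8 × 0.6 × 3 = 0.072C.
- Against 2C: 0.010 / 2 = 0.5% and 0.072 / 2 = 3.6%.

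**Cross-check on different assumptions**
- All deaths in hospital, terminal admission at average cost, 8 admissions a year, mortality difference 5 to 10 points, fixed share 30% to 70%.
- Low: 0.05 × 0.3 / 8 = 0.2% of annual cost. High: 0.10 × 0.7 / 8 = 0.9%.
- On 8C a year these are 0.015C and 0.07C, the same order as above.

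**The case against.** The strongest reply is that this is a condensed article. The choice of ratio, the pairing of costs with effects and the interval method may properly sit in a full protocol or analysis plan. The article still commits to cost-effectiveness, nowhere says that only costs will be compared, and specifies the effects needed. This stands as far as it goes: the lack of a named ratio or interval method is not the point. What remains is that the article does state the endpoint, and that endpoint differs from the objective. A reader might infer that objective iii will go unanswered. The documents do not support that, because item iii also covers efficacy and the effect data are collected.

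A reader might also infer that a death registers as a saving. If costs were simply summed, with deaths at six months on average, a 5-point mortality difference would remove 0.05 × 4C = 0.2C, or 10% of 2C. An expensive terminal admission would offset part of this: at 3 times average cost with 80% of deaths in hospital, 0.05 × 0.8 × 2C = 0.08C, leaving 0.12C (6%). But this arises only if the general allowance for survival is not applied to costs, and the article does not say that. How it applies is simply left open.

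Nor would harm be hidden. Days alive and out of hospital counts death as lost time, the Statistical analysis section analyses all-cause mortality, and the monitoring committee reviews deaths.

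On the fixed-cost wording, both total-cost formulas add fixed costs without a survivor exception, so an analyst may well cost fatal admissions in full. But the formulas use the term just defined, so they do not correct the definition.

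**Conclusion.** The point holds in a limited form. The cost-effectiveness part of objective iii has no matching endpoint: the endpoint list and the section it cites stop at costs. Separately, the fixed-cost definition is limited to surviving patients and, applied literally, under-costs admissions that end in death.

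The numerical consequence of the definition is small: about 0.01C to 0.07C per participant, or 0.5% to 3.6% of the planned gross saving of two admissions, for a 5-point mortality difference. The mortality difference, place of death, fixed share and relative cost of a terminal admission are all assumptions. Patients expected to live 12 months or less are excluded, so deaths may be few. The mismatch has no numerical size; it limits what the economic result can say if the package works at a net cost. Both matters concern a secondary objective and leave the primary endpoint untouched.

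**What to change.** 1. In Health economic analyses, reword the definition so that fixed costs apply to every admission, including those ending in death, whatever the length of stay.
2. Align secondary endpoint vi and Health economic analyses with objective iii: set incremental cost against an effect already collected, either admissions avoided or days alive and out of hospital, in the same intention-to-treat participants over 12 months. Days alive and out of hospital has the advantage of counting death as lost time. The interval method can be left to the analysis plan.
3. State how the allowance for death and loss to follow-up in Outcome measures applies to costs, treating the two separately: after a death no further cost arises, whereas after loss to follow-up the cost is unknown. If 12-month totals are used, a death still shortens the period in which cost accrues, so the cost difference must be read together with the effect measure.

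This costs a few sentences and needs no new data. The downside is that the cost-effectiveness estimate will have a wide interval and may look less favourable than a bare cost difference.

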**Fig. 3 Fig3:**
[figure not shown]
The intervention process

The intervention team will facilitate the following activities following discharge through liaison with the participant, family and/or primary health care provider:Telephone case conference with patient and family between day 3 and 5 of discharge. Telephone contact was chosen over home visits given the potential remoteness of our patient population and the inherent difficulties in providing a home based service post discharge. This semi structured interview with focus on how the patient is coping post discharge, any complications/new problems, medication supply, adherence and side effects, a reminder of upcoming reviews and any potential barriers to attending these appointments. The researcher will provide advice and modify the management plan depending on outcomes of this phone interview.Telephone case conference with primary care provider between day 1 and 5 post discharge. The researcher will provide the primary care provider with a summary of the admission and discharge plan and an opportunity to clarify any confusion. The researcher will also check that the primary care provider received the written discharge plan and that the patient has a review appointment booked.Participant primary health care review within 7 days following hospital discharge.Support for participants if they return to hospital for outpatient review and/or investigations to encourage ambulatory service attendance and to consolidate understanding of management plans and expectations.

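### The intervention is costed on team time with each patient, which read literally omits non-contact work and interpreters and so understates the intervention's cost

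*Protocol article*

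**What the plan says.** Objective iii of the protocol article is to "Evaluate the efficacy and cost-effectiveness of this tailored case management-based approach", and health care costs are secondary endpoint vi.

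The Health economic analyses section opens with a general rule: "The use of all health care resources will be measured and multiplied by the respective unit costs". It then gives three specific rules:

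- **Hospital admissions.** National Weighted Activity Units are to allow "standardisation and categorisation of each readmission episode into fixed and variable costs". The emergency department enters here: "Fixed costs will include components for the emergency department, pathology, imaging, allied health professional input, pharmacy, critical care".
- **The intervention.** "Costs for providing the intervention will be calculated based on time spent by all team members with each patient". No other intervention cost item is named.
- **Primary care.** Visits are multiplied by a standard GP cost.

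The section on participants assigned to the intervention group describes what has to be costed: seven inpatient components, provided at every admission, and four after discharge. The team is a medical officer, a nurse, an Aboriginal Health Practitioner and a pharmacist. After discharge the package includes "Telephone case conference with primary care provider between day 1 and 5 post discharge" and "Support for participants if they return to hospital for outpatient review and/or investigations to encourage ambulatory service attendance".

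**The concern.** The specific rule for the intervention does not match the intervention described. Coordination and liaison are central to the package, and most of that work is done with other professionals while the patient is elsewhere. A rule tied to time with the patient captures the bedside interview, the education, the medication review and the call to the patient, but on its plain wording not the rest.

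The error would have a known direction for this cost item. The control arm receives usual discharge planning only, so uncosted package work arises solely in the intervention arm and makes the package look cheaper than it is. By the protocol's own account the cost is not trivial: the 1:2 allocation was chosen because of the resources the intervention needs, and the Discussion looks ahead to health care savings.

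There is also a practical risk. Staff filling in time logs could follow either a narrow or a broad reading of the sentence, and non-contact time not logged as it happens is hard to reconstruct.

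**Working it through.** The plan gives no cost figure, so there is nothing to reproduce. The check sets the costing rule against the package and then examines the direction of any bias.

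**1. Components against the rule** (intervention-group section; 7 + 4 = 11 components)

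| Component | Done with the patient? |
|---|---|
| Needs-based interview | Yes |
| Coordination of referrals | Mainly no |
| Education of participant and family | Yes, with interpreters from outside the team |
| Medication review and bedside education | Largely yes |
| Case conference with ward staff | Mainly no |
| Primary-care liaison and discharge summaries | No |
| Written discharge plan | Partly |
| Telephone call to patient and family | Yes |
| Telephone call to primary care provider | No |
| Primary care review within 7 days | A primary care visit, costed under the GP rule; arranging it is non-contact |
| Support at outpatient return visits | Yes |

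Four of the 11 (36%) involve little or no patient contact, and a fifth is partly non-contact. This counts components, not hours.

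**2. Repetition.** The inpatient components recur at each admission. The Sample size section gives a mean of 8 admissions a year and a target reduction of 25%, so 8 × 0.75 = 6 a year in the intervention arm if the target is met. The three mainly non-contact inpatient components would then recur about 3 × 6 = 18 times per participant-year, not counting the index admission. Any undercount accumulates.

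**3. Size of the undercount.** If f is the share of team time that is non-contact, and time is valued alike, true cost ÷ costed figure = 1/(1 − f). The documents give no f. As an assumed range:

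- f = 0.4: 1/0.6 = 1.67
- f = 0.6: 1/0.4 = 2.5

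This ratio covers team time only, before interpreters. It cannot be set against the saving from the targeted two fewer admissions (8 × 0.25), because no unit costs are given.

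**4. Direction over all cost items.** Suppose uncosted intervention work, emergency attendances without admission and outpatient attendances were all left out. The bias per patient, positive when it favours the intervention, is

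B = I + dED × cED + dOPD × cOPD,

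where I is the uncosted intervention work, dED and dOPD are the intervention-minus-control differences in visits, and cED and cOPD are unit costs. All values below are assumptions, with cED = 600 and cOPD = 300 in arbitrary currency units:

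| I | dED | dOPD | B |
|---|---|---|---|
| 0 | −3 | 0 | −1800 |
| 500 | −1 | 0 | 500 − 600 = −100 |
| 500 | 0 | +1 | 500 + 300 = +800 |
| 1500 | +1 | +3 | 1500 + 600 + 900 = +3000 |

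The term I is never negative. The emergency term is negative if attendances fall, as the Hypothesis section's expected reduction in health care utilisation suggests. The outpatient term is positive only if attendances rise. The sign of B is therefore not fixed.

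**The case against.** The best defence is that the sentence is a summary and can be read as staff time per patient case. The package is described as case-based, conferencing and liaison are named team tasks, and nothing in the section limits costing to face-to-face contact. That reading is possible and would bring in non-contact team time. It does not clearly bring in interpreters, and since both readings are open it is a reason to fix the wording.

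A second defence is that interpreters may already sit in the inpatient per diem, which includes non-clinical staff, or under the general rule. The documents do not say so. A per diem that depends on length of stay would also give both arms the same amount for the same stay, so it would not show extra interpreter use in one arm.

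Third, the size rests on an assumed share. This stands: 1.67 to 2.5 illustrates the formula and is not an estimate for this trial.

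Two stronger readings are tempting, and the documents support neither. A reader might infer that emergency attendances without admission and outpatient visits have no costing rule. The opening sentence of the section covers every health care resource, and emergency attendances are counted as a secondary endpoint. Only a specific formula is absent, and a journal article may leave that to the full plan. A reader might also infer that objective iii as a whole would be answered in the intervention's favour. That does not follow: leaving out emergency visits would work against the intervention if those visits fall as hypothesised.

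**Conclusion.** The point holds for the intervention's own cost. On its literal wording the rule omits work that the protocol makes part of the package, and interpreter input, which is not team time. Both omissions lower the apparent cost of the intervention arm, so the bias in that component of objective iii and secondary endpoint vi favours the intervention. This rests on two things: that the sentence is applied as written, and that the omitted work is additional to usual care, as the intervention section says.

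The size is unknown without a non-contact share, and the net bias over all cost items is not determined. The documents do not show that a true net cost would be turned into an apparent saving. The primary endpoint is unaffected.

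**What to change.** In the Health economic analyses section, reword the intervention sentence so that it costs all team time spent on each participant's behalf, contact and non-contact: referral coordination, case conferences, liaison, discharge summaries and plans, and calls to providers. Add interpreter time as a separate item. As a sensitivity analysis, use total team salary cost divided by the number of intervention participants; this needs no time log and can be done even if recruitment has begun.

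In the same section, state that the general rule applies in both arms to emergency attendances not ending in admission, which are already counted, and to outpatient attendances, which the intervention is meant to encourage.

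The cost is a time-log column for non-contact work, a record of interpreter time and outpatient attendances, and a less favourable intervention cost.
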